#### Study monitoring

Only in centers requiring such monitoring, a clinical research associate will monitor the study. All monitoring visitations will be scheduled at mutually agreeable times, periodically during the study at a frequency deemed appropriate. These visits will be conducted to evaluate the progress of the study, to ensure that the rights and well-being of the subjects are protected, to check that the reported clinical study data are accurate, complete, and verifiable from source documents, and if the conduct of the study is in compliance with the approved protocol and amendments, good clinical practice, and applicable national regulatory requirements. A monitoring visitation will include a review of the essential clinical study documents (regulatory documents, case report forms, source documents, subject informed consent forms, etc.) as well as discussion on the conduct of the study with the investigators. The investigators should be available during these visitations to facilitate the review of the clinical study records and to discuss, resolve, and document any discrepancies found during the visitation. Auditing will be performed at 50% of the inclusions and at the end of the study. The Trial Steering Group will review data at 50% of the inclusions.

## Statistical analysis

Primary and secondary endpoints will be cross checked with data from primary sources and a blinded adjudication committee will check them against the definitions, which are established before the start of this study. Frequencies will be presented for dichotomous data. The primary endpoint Clavien-Dindo score ≥ 3 complications will be tested for non-inferiority using the chi-square test. The distribution of variables will be determined using several plots (boxplot, Q-Q plot, and histogram) and the Kolmogorov-Smirnov, Shapiro-Wilk, and Levene’s tests. For comparison of normally distributed continuous variables, the independent samples *t*-test will be used and values will be expressed as means (standard deviations). Continuous non-normally distributed variables will be compared using the Mann-Whitney *U* test and values will be expressed as medians (interquartile ranges). Categorical variables will be compared by chi-square or Fisher’s exact test as appropriate, and values will be expressed as proportions. A two-tailed *p*-value <0.05 will be considered statistically significant. Where possible, risk ratios with 95% confidence intervals will be reported. For the primary study outcome, a two-sided 95% confidence interval will be reported. Time to event endpoints, such as survival, will be calculated using Kaplan-Meier estimations. A Cox regression analysis will be performed to investigate predictors of postoperative survival. All parameters with a *p*-value <0.1 in a univariable analysis are included in the multivariable Cox regression analysis. Additionally, multivariable analyses are performed to determine predictors for primary and secondary study outcomes, for example R0 resection, the occurrence of postoperative pancreatic fistula. Intraoperative details and primary endpoint of this study are expected to be complete. All data entries should be sent to the project leader immediately after the final examination. In case of missing data, explanation should be given to the project leader. For subjects who are lost to follow-up, a sensitivity analysis will be performed to determine best-case/worst-case scenarios. A detailed statistical analysis plan will be drafted prior to database lock. Despite all prior preventive measures taken, a complex multinational trial may still evoke unforeseen situations after database lock that threaten data integrity and can only be resolved by unlocking the database prior to the final analysis. For purpose of transparency and reproducibility, the statistical analysis plan will therefore also describe the procedure to be followed when such situations arise.

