### Sample size calculation

The PANDORINA trial is as a non-inferiority randomized trial, hypothesizing that the outcome (i.e., postoperative complications Clavien-Dindo score ≥ 3 and, secondarily, clinically relevant POPF, grades B and C) in patients undergoing DP without prophylactic abdominal drainage are non-inferior to those of patients with routine prophylactic abdominal drainage after surgery. The sample size is calculated according to the formula (available at https://www.sealedenvelope.com/power/binary-noninferior/):$$n=f\left(\alpha, \beta \right)\times \left[{\pi}_{\mathrm{s}}\times \left(100-{\pi}_{\mathrm{s}}\right)+{\pi}_{\mathrm{e}}\times \left(100-{\pi}_{\mathrm{e}}\right)\right]/{\left({\pi}_{\mathrm{s}}-{\pi}_{\mathrm{e}}-d\right)}^2$$ where *π*_s_ and *π*_e_ are the true percent “success” in the “drain” and “no drain” groups respectively.$$F\left(\alpha, \beta \right)={\left[{\varPhi}^{-1}\left(\alpha \right)+{\varPhi}^{-1}\left(\beta \right)\right]}^2$$

And *φ*^−1^ is the cumulative distribution function of a standardized normal deviate.

Patients recruited in the PANDORINA trial will be randomized within the referred Institute with a 1:1 allocation ratio. The primary endpoint of the present trial is the rate of Clavien-Dindo ≥3 major complications, following the assumption: 2.5% one-sided significance level (*α*), 80% power (1−*β*), and a non-inferiority level of 8%. The expected success percentage in the intervention arm (no prophylactic abdominal drainage) of 77% and a success percentage in the control group of 70% (prophylactic abdominal drainage, based on the multicenter LEOPARD trial with a majority of minimally invasive procedures) [21]. The needed number of patients was calculated with a sealed envelope: a total of 272 patients are required. Including a 3% of possible drop-out after randomization, the total required sample size is 282 patients (141 patients per arm).

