### Study parameters/endpoints

#### Main parameters/endpoint

Primary endpoint is the rate of Clavien-Dindo score ≥ 3 complications [26].

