### Randomization and treatment allocation

Eligible patients for the study will be identified at the outpatient clinic and in this stage informed consent will be obtained; the randomization will take place directly after start of the operation, when the decision is made to proceed with the resection. The surgeon performing the operation will call the study coordinator to perform the randomization in Castor EDC. Patients will be analyzed according to the allocated treatment, as per intention-to-treat principles. If during the operation is chosen not to act conform the randomization, specification of this choice is required. A per-protocol analysis will also be performed for the primary endpoint.

A data safety monitoring committee will assess safety endpoints per 50 randomized patients. All patients will be randomized centrally using an online computer-controlled permuted-block randomization module in a 1:1 ratio. The block sizes itself will be subject to random variation with block sizes varying from 4 to 8 patients. The entire randomization will be concealed to all involved investigators except the trial coordinators. Patients will be coded by a numeric randomization code and the principal investigator will be the only one with access to it and investigators and patients are not blinded. Patients will be stratified according to high or low risk and minimally invasive and open procedure. The source data will be stored digitally and will be kept by the project leader for 15 years after the inclusion of the last patient.

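### The test named for the primary non-inferiority question is a chi-square test, which does not use the 8-point margin, and the promised 95% confidence interval is not tied to that margin

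*Protocol article*

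**What the plan says.** The Sample size calculation states the design: "The PANDORINA trial is as a non-inferiority randomized trial". It uses a "2.5% one-sided significance level", 80% power and "a non-inferiority level of 8" percent. Expected success is 77% without a drain and 70% with one, that is, 23% and 30% complications. The printed formula subtracts the margin from a difference of two percentages, so the margin is an absolute risk difference. The endpoint is binary: "Primary endpoint is the rate of Clavien-Dindo score ≥ 3 complications".

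The Statistical analysis section says that these "complications will be tested for non-inferiority using the chi-square test". It does not mention the 8% margin, a null hypothesis shifted by the margin, or a rule for concluding non-inferiority. It gives a general two-tailed 5% significance rule, followed by "Where possible, risk ratios with 95% confidence intervals will be reported". A separate sentence promises a two-sided 95% confidence interval for the primary outcome, without naming its scale. A detailed SAP is to be written before database lock.

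Grade B/C POPF is also sized for non-inferiority, with the same alpha, power and 8% margin, so that both endpoints can support a conclusion. The Statistical analysis section gives it no non-inferiority rule.

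**The concern.** The trial is sized to exclude a harm of 8 points or more, but the test named for that purpose asks whether the two rates are equal. A non-significant chi-square result does not show that harm is below 8 points, and a significant one is not needed for non-inferiority. The planned 2.5% error rate and 80% power therefore do not belong to the named test.

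The promised interval could answer the question, but as written it is not connected to it. An absolute margin also has no fixed risk-ratio equivalent. Eight points is a risk ratio of 38/30 = 1.27 at a 30% control rate, but 28/20 = 1.40 if the control rate were 20% (an illustrative value). With the scale and the comparison left open, the choice could be made after the results are seen, in a trial whose investigators are not blinded.

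**Working it through.** **Inputs**, all from the Sample size calculation: success 70% (drain) and 77% (no drain), margin 8 points, one-sided alpha 2.5%, power 80%, 141 patients per arm after allowance for drop-out.

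**1. Reproduce the plan's figure.** With f = (1.960 + 0.842)² = 7.849, the printed formula gives

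n = 7.849 × [70×30 + 77×23] / (70 − 77 − 8)² = 7.849 × 3871 / 225 = 135.04, so 136 per arm and 272 in total, as stated.

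For POPF: 7.849 × [75×25 + 81×19] / (75 − 81 − 8)² = 7.849 × 3414 / 196 = 136.7, so 137 per arm and 274 in total, as stated. Both figures therefore belong to a test against an absolute 8-point margin.

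**2. Interval compared with the margin, 141 per arm, design assumption.** The standard error is √[(0.21 + 0.1771)/141] = 0.0524. Power = Φ(0.15/0.0524 − 1.96) = Φ(0.90) = 81.7%; exact binomial enumeration gives 81.5%. At a true difference equal to the margin (complications 30% vs 38%), the rule passes in 2.5% of trials. This agrees with the stated alpha and power.

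**3. Chi-square test of equality, same trial, design assumption.** The pooled rate is 0.735, so the null standard error is √(2 × 0.735 × 0.265/141) = 0.0526 and the critical difference is 1.96 × 0.0526 = 0.103. Power = Φ((0.07 − 0.103)/0.0524) = Φ(−0.63) = 26.4%; exact, 26.8%. Reaching 80% would need 623 per arm.

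**4. Chi-square test at a true 8-point harm (30% vs 38%).** The pooled success rate is 0.66, the null standard error √(2 × 0.66 × 0.34/141) = 0.0564, the critical difference 0.111 and the unpooled standard error 0.0562. The chance of significance is about Φ((0.08 − 0.111)/0.0562) = 29%, so about 71% of trials are non-significant. Exact enumeration gives 70.1% at 141 per arm; simulation at 137 per arm gives 71%.

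| Truth (complications, drain vs no drain) | Chi-square significant | Chi-square non-significant | 95% CI upper limit below +8 |
|---|---|---|---|
| 30% vs 23% (design) | 26.8% | 73.2% | 81.5% |
| 30% vs 30% | 5.1% | 94.9% | 31.4% |
| 30% vs 38% (margin) | 29.9% | 70.1% | 2.5% |

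(Exact, 141 per arm.)

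**5. Illustrative outcomes, 141 per arm, 42 complications with a drain.**

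| Complications without drain | Chi-square p | Risk difference, no drain minus drain (95% CI, points) | Against +8 |
|---|---|---|---|
| 32 | 0.18 | −7.1 (−17.3 to +3.1) | non-inferior |
| 42 | 1.00 | 0 (−10.7 to +10.7) | not shown |
| 53 | 0.17 | +7.8 (−3.2 to +18.8) | not shown |

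The outer rows have nearly the same p-value and opposite conclusions. In the middle row the arms are identical, and non-inferiority is still not shown.

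The calculations use the Pearson chi-square without continuity correction and the unpooled Wald interval, which matches the protocol's formula.

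**The case against.** A reader might infer that the stated analysis can neither establish nor refute non-inferiority. The document does not support that. The two-sided 95% interval promised for the primary outcome matches one-sided 2.5%, and on the risk-difference scale against 8 points it would decide the question with the planned power. A significant chi-square favouring no drain would also support non-inferiority, which happens in about 27% of trials under the design assumption.

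A reader might also take 70% as the plan's false-positive rate. It is not, because the article nowhere says that a non-significant chi-square will be read as non-inferior. The figure shows what that reading would cost. The reading is not far-fetched: the article's Discussion relays non-significant differences in the earlier randomized trial of drain omission as comparable outcomes, and its benefit and risk section treats that trial as having shown safety. That does not establish how this trial would be read.

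Two other defences have some force. A score statistic with a shifted null exists and could be what was meant, but the text gives no sign of it. The scale of the interval is a detail that a SAP commonly supplies and would not be a finding alone. The general 5% rule and the risk-ratio sentence also need not be primary-endpoint rules, and placing POPF under the generic categorical tests is an inference.

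Absence of a stratified analysis, or of required agreement between the intention-to-treat and per-protocol results, is not a fault shown here. The article does plan a per-protocol analysis: "A per-protocol analysis will also be performed for the primary endpoint".

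What the objections leave standing is the sentence that names the test. It is a positive statement, and a SAP could be right only by departing from it.

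**Conclusion.** The point holds in this form: the article names an equality test as its non-inferiority test, and the interval that could do the work is linked neither to the risk-difference scale nor to the 8-point margin. This must be corrected because it concerns the primary conclusion.

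The size depends on how the chi-square would be used, which the article does not say. Taking non-significance as success raises the error at the margin from 2.5% to about 70%. Requiring significance lowers the chance of success under the design assumption from 81–82% to 26–27%. These figures assume 137 to 141 evaluable patients per arm and the protocol's 30% control complication rate.

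**What to change.** Replace the chi-square sentence in the Statistical analysis section, and carry the same text into the SAP:

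*Non-inferiority is concluded if the upper limit of the two-sided 95% confidence interval for the absolute risk difference (no drain minus drain) in Clavien-Dindo ≥ 3 complications is below +8 percentage points.*

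A one-sided 2.5% score test against the same margin would be an acceptable equivalent. Apply the same rule to grade B/C POPF with its stated 8% margin. Report chi-square p-values and risk ratios as supportive only.

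The cost is a wording change, to be made before database lock. It needs no new data and no change in sample size, since the stated 272 and 274 already correspond to this rule.

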### Need for a randomized trial

Current published series on prophylactic abdominal drainage after DP are mostly retrospective, only one multicenter randomized trial is available and this did not stratify patients according to their risk of POPF and did not use a standardized technique of transecting the pancreas [2]. It could be that outcomes of prophylactic abdominal drainage differ between patients with low and high risk of POPF after DP.

PANDORINA is a binational multicenter, randomized controlled non-inferiority trial with the primary objective to evaluate the hypothesis that omitting prophylactic abdominal drainage after DP does not worsen the risk of postoperative Clavien-Dindo score ≥ 3 complications (e.g., reinterventions, catheter drainage, wound infections, postoperative pancreatic hemorrhage, feeding tube placement) [18, 19].

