The most relevant secondary endpoint is the rate of clinically relevant POPF (grades B and C). The sample size was calculated with the following assumption: 2.5% one-sided significance level (*α*), 80% power (1−*β*), and a non-inferiority level of 8%. The expected success percentage in the intervention arm (no prophylactic abdominal drainage) is 81%, and a success percentage in the control group (prophylactic abdominal drainage) is 75%. This difference of 6% less grade B/C POPF without abdominal drainage is based on the Van Buren trial, and the baseline risk of 25% grade B/C POPF is based on the recently published distal fistula risk score (D-FRS), a combined Dutch/Verona multicenter study [22]. The needed number of patients was calculated with sealed envelope: a total of 274 patients. Including a 3% of possible drop-out after randomization, the total required sample size is 282 patients (141 patients per arm).

Based on the second (slightly lager) sample size calculation, we will include 282 patients so that conclusions can be drawn for both endpoints.

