## Conclusion

PANDORINA is a binational multicenter, randomized controlled non-inferiority trial with the primary objective to evaluate that omitting prophylactic abdominal drainage after DP does not worsen the risk of postoperative Clavien-Dindo score ≥ 3 complications [18, 19]. Additional to the current literature, the PANDORINA trial makes prespecified fistula risk groups and guarantees homogenous stump closure.

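### The primary non-inferiority test is an unstratified chi-square although randomisation is stratified by fistula risk: a small, conservative loss of precision that costs almost nothing to recover

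*Protocol article*

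**What the plan says.** All references are to the Protocol article.

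- **Randomisation.** The Stratification section stratifies by preoperative POPF risk (high or low) and by annual hospital volume. The section on randomization and treatment allocation stratifies by POPF risk and by minimally invasive versus open procedure. The two agree on risk and differ on the second factor.
- **Primary analysis.** The Statistical analysis section says that Clavien-Dindo grade 3 or higher is tested for non-inferiority by chi-square. No stratification or adjustment is named.
- **Other categorical outcomes**, which include grade B/C POPF: "Categorical variables will be compared by chi-square or Fisher’s exact test as appropriate, and values will be expressed as proportions".
- **Multivariable models** in the same section look for predictors of the primary and secondary outcomes. They are not described as adjusted treatment comparisons.
- **Role of the risk groups.** The section on the need for a randomized trial says "It could be that outcomes of prophylactic abdominal drainage differ between patients with low and high risk of POPF after DP". The Conclusion lists among the trial's additions that "the PANDORINA trial makes prespecified fistula risk groups".
- **Statistical analysis plan.** One is announced, to be written before database lock. It is not available here.

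**The concern.** Randomising within strata of a prognostic factor removes chance imbalance on that factor, so the treatment difference varies less from trial to trial. A crude two-group comparison does not use this: its standard error still contains the between-stratum variation that the design removed. The interval comes out wider than it need be, and in a non-inferiority trial a wider interval makes it harder to exclude the margin.

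At stake is a little power. There is not much to spare, because the planned 80% depends on the no-drain arm being 7 points better. With 70% success in both arms and 137 per arm, power at the 8-point margin would be about 30%.

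The announced analysis plan does not remove the point. The protocol has not left the primary test open; it names one that does not match its randomisation.

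**Working it through.** **Inputs from the Sample size calculation section.** "2.5% one-sided significance level"; 80% power; "a non-inferiority level of 8" percent; "The expected success percentage in the intervention arm (no prophylactic abdominal drainage) of 77% and a success percentage in the control group of 70" percent; for grade B/C POPF, 81% without a drain, and "a success percentage in the control group (prophylactic abdominal drainage) is 75" percent; "with a 1:1 allocation ratio".

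**Assumptions (not in the documents).** Half the patients are high risk. The event rate differs between risk groups by g = 10, 20 or 30 points, equally in both arms. The risk difference is the same in each group and the strata are balanced. The second factor is ignored. Evaluable n = 137 per arm (274/2).

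**Step 1: the plan's own figures.** n per arm = (1.960 + 0.842)² × [p₁(1−p₁) + p₂(1−p₂)] / (difference + margin)², where the squared sum is 7.849.

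- Primary: 0.70×0.30 + 0.77×0.23 = 0.3871; 7.849 × 0.3871 / 0.15² = 135.04, so 136 per arm and 272 in total, as stated.
- POPF: 0.75×0.25 + 0.81×0.19 = 0.3414; 7.849 × 0.3414 / 0.14² = 136.7, so 137 per arm and 274 in total, as stated.

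Both figures come from the unstratified formula, so the planned size does not rely on stratification.

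**Step 2: variance with strata.** With half the patients in each group, stratifying removes 2 × 0.5 × 0.5 × g² = 0.5g² from the variance term V. Crude V = 0.3871; crude SE = √(0.3871/137) = 0.0532.

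| Gap g | Stratified V | Ratio to crude | Stratified SE | Interval narrower by |
|---|---|---|---|---|
| 10 points | 0.3821 | 98.7% | 0.0528 | 0.6% |
| 20 points | 0.3671 | 94.8% | 0.0518 | 2.6% |
| 30 points | 0.3421 | 88.4% | 0.0500 | 6.0% |

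**Step 3: power.** The estimate varies with the stratified SE in both analyses; the crude test sets its limit with the crude SE.

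- Crude: Φ[(0.15 − 1.96 × 0.0532) / SE_strat]. Stratified: Φ[0.15 / SE_strat − 1.96].
- Gap 10: 80.7% against 81.1%, a gain of about 0.3 points before rounding.
- Gap 20: 81.2% against 82.6%, a gain of 1.4 points. n per arm for 80% power falls from 136 to 129.
- Gap 30: 82.0% against 85.1%, a gain of about 3 points.

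**Step 4: true one-sided error of the crude test.** At the margin the event rates are 30% with a drain and 38% without, so crude V = 0.21 + 0.2356 = 0.4456. Error = 1 − Φ[1.96 × √(0.4456 / (0.4456 − 0.5g²))].

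- Gap 10: V ratio 0.4456/0.4406 = 1.011, error 0.024.
- Gap 20: 0.4456/0.4256 = 1.047, error 0.022.
- Gap 30: 0.4456/0.4006 = 1.112, error 0.019.

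All are below 0.025.

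**Step 5: what estimates by risk group could show.** For a group holding 30%, 50% or 70% of patients (about 41, 68 or 96 per arm), with the overall rates applied inside the group:

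- 95% half-width = 1.96 × √(0.3871 / n): about 19, 15 and 13 points.
- Power for non-inferiority within the group at the 8-point margin: about 34%, 51% and 66%.
- Difference in risk difference between groups detectable with 80% power: 2.80 × √[0.3871 × (1/n_high + 1/n_low)], about 30 points at an even split and 33 points at a 30/70 split.

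**The case against.** The strongest defence is that the chosen test matches the sample size. Both stated totals reproduce without stratification, crude power is at or above 80% under the planning assumptions, and the error runs in the safe direction. All of that stands. The gain also rests on an assumed prognostic gap, and at 10 points it is negligible.

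A reader might infer more: that the trial never estimates the drain effect by risk group, leaves unanswered the question it was built for, and could hide harm in high-risk patients behind an overall result. The documents do not support this.

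- The stated primary objective is overall non-inferiority. A possible difference by risk is given as rationale, and no section makes it an objective or endpoint.
- Estimates by subgroup are commonly left to an analysis plan, and one is announced. All that can be said is that this protocol states no such estimate.
- The multivariable models cover the primary outcome, give their targets only as examples and do not list covariates.
- At this size, estimates by risk group would be too imprecise to settle the matter (step 5).

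The defence does not reach the primary test, which the protocol specifies without strata.

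**Conclusion.** The point holds as a modest improvement. The protocol fixes an unstratified primary test under stratified randomisation. This overstates the standard error by an amount that depends on how strongly risk group predicts Clavien-Dindo grade 3 or higher. Under the assumptions above, the cost runs from practically nothing at a 10-point gap to about 3 power points at 30. In the cases computed with a 30/70 split the cost is slightly smaller: at a 30-point gap, power is 81.8% crude against 84.4% stratified.

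The type I error stays below its nominal level, so nothing here favours a false claim of non-inferiority, and the planned power is reached if the protocol's success rates are right. The case for change is that the precision is nearly free. The absence of estimates by risk group is secondary: worth filling because the risk groups are presented as the trial's novelty, but not a demonstrated omission from the full plan.

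**What to change.** 1. **Reconcile the second stratification factor.** The Stratification section (hospital volume) and the section on randomization and treatment allocation (minimally invasive versus open) cannot both be complete as written. Confirm from the randomisation system which factors were used. Until then the strata cannot be coded.
2. **Replace the crude primary test.** Use a stratified risk difference with a two-sided 95% confidence interval set against the 8-point margin, for example with Mantel-Haenszel weights and the factors actually used. Do the same for grade B/C POPF. The crude difference can be kept as a sensitivity analysis.
3. **Optional.** Report the risk difference with its 95% interval in high-risk and low-risk patients, plus one treatment-by-risk interaction test. Label these descriptive and make no separate non-inferiority claims.

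The cost is one check of the randomisation settings, a few sentences in the analysis plan before database lock, and a few lines of code. No extra patients or data are needed, provided the factors used at randomisation were recorded.

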## Background

### Clinical background

The debate on routine prophylactic abdominal drainage after partial pancreatectomy has been ongoing for decades [1, 2]. Most series combine outcomes of pancreatoduodenectomy and distal pancreatectomy (DP) or focus on pancreatoduodenectomy only. There is, however, an essential difference between POPF in DP and pancreatoduodenectomy. Whereas POPF after pancreatoduodenectomy, by definition, involves infection due to anastomotic dehiscence between pancreas and small bowel, a POPF after DP is, by definition, initially sterile since no anastomoses are created. Prophylactic abdominal drainage after DP could therefore also introduce bacteria and cause drain-induced infections [3].

Recent reviews underline the need of data regarding abdominal drainage in DP [4–6]. In high-volume centers, DP has a very low mortality (0–2%) but the morbidity rate remains high (24 to 56%) with postoperative pancreatic fistula (POPF) as most common complication (0% to 61%) and cause of further complications [7–14]. Unfortunately, the risk of POPF after DP has proven difficult to predict [15]. Prophylactic abdominal drainage after DP allows for evacuation of pancreatic fluid, in case of POPF, but a drain could theoretically also induce infection, especially when left in place for prolonged periods [6, 16] or even bleeding due to vascular erosion [1]. In patients with a leak at the pancreatic transection margin, without a drain, a sterile and asymptomatic pseudocyst (i.e., no infected collection requiring no intervention) could occur [17].

A randomized controlled trial (RCT) is mandatory to determine whether patients are better off without the use of prophylactic abdominal drainage after DP.

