#### Data collection

Baseline characteristics will be recorded before randomization. The required clinical data, i.e., primary and secondary outcomes, will be collected after randomization, i.e., from hospitalization up to 6 months postoperatively using standardized case report forms, and in Dutch centers according to the mandatory Dutch Pancreatic Cancer Audit which is coded. All complications will be scored using the Clavien-Dindo score of surgical complications (see Additional file 1).

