### Follow-up of subjects withdrawn from treatment

All subjects will be analyzed according to intention-to-treat principles and follow-up will be 6 months after DP.

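### The planned multivariable Cox model for survival, with uncapped p<0.1 entry, has too few expected deaths to support it, and survival and R0 resection are not in the outcome list

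*Protocol article*

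**What the plan says.** The Statistical analysis section treats survival as a time-to-event endpoint to be described by Kaplan-Meier estimates and then adds: "A Cox regression analysis will be performed to investigate predictors of postoperative survival". The entry rule follows: parameters with a p-"value <0.1 in a univariable analysis are included in the multivariable Cox regression analysis". No candidate list and no maximum number of terms is given. The next sentence plans further multivariable analyses of the primary and secondary outcomes and illustrates these with "for example R0 resection" and pancreatic fistula.

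Elsewhere in the article:

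- The primary endpoint is Clavien-Dindo grade 3 or higher (Main parameters/endpoint). The secondary list contains death only as in-hospital and 90-day mortality (Secondary parameters/endpoint). Neither section lists survival time or R0 resection. R0 is also absent from the baseline items under Other study parameters.
- Outcome data are collected "from hospitalization up to 6 months postoperatively using standardized case report forms" (Data collection), and "follow-up will be 6 months after DP" (Follow-up of subjects withdrawn from treatment).
- On mortality, Clinical background says only: "In high-volume centers, DP has a very low mortality (0–2"%).
- On size, Sample size calculation says: "the total required sample size is 282 patients (141 patients per arm").

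**The concern.** What a Cox model can support depends on the number of deaths, not the number of patients. A short follow-up after an operation with low stated mortality will produce few. An automatic p<0.1 screen makes this worse. With few events, a covariate passes only if its observed effect is very large, so the retained coefficients are biased away from zero and their intervals are too narrow. Followed as written, the plan would report predictors of survival that mostly reflect chance and selection.

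The second issue is consistency. The analysis section treats survival and R0 resection as outcomes, while the endpoint sections do not list them. A reader cannot tell from this article which outcomes are prespecified.

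**Working it through.** **1. Denominator.** The sample size formula in the article, n = f(α, β) × [πs(100 − πs) + πe(100 − πe)] / (πs − πe − d)², with one-sided α 2.5%, power 80%, margin 8 and f = (1.960 + 0.842)² = 7.849, gives:

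- Primary endpoint, 70% v 77%: 7.849 × (2100 + 1771) / 15² = 135.04, so 136 per arm and 272 in total, as stated.
- POPF, 75% v 81%: 7.849 × (1875 + 1539) / 14² = 136.71, so 137 per arm and 274 in total, as stated.
- Drop-out: 274 × 1.03 = 282.2, against the stated 282.

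The document states no expected number of deaths. 282 is used as the denominator below.

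**2. Expected deaths.** Deaths = 282 × rate. Rates of 0–2% are the document's; 3–10% are assumptions about 6-month mortality. Ten events per parameter is a common rule of thumb, also assumed here; five is shown as a laxer alternative.

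| Rate | Source | Deaths | Parameters at 10 events each | Parameters at 5 events each |
|---|---|---|---|---|
| 0% | document | 0 | 0 | 0 |
| 2% | document | 5.6 | 0.6 | 1.1 |
| 3% | assumed | 8.5 | 0.8 | 1.7 |
| 5% | assumed | 14.1 | 1.4 | 2.8 |
| 8% | assumed | 22.6 | 2.3 | 4.5 |
| 10% | assumed | 28.2 | 2.8 | 5.6 |

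If the true rate is 2%, the binomial chance of 7 or more deaths is 0.34 and of 10 or more is 0.06.

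**3. Precision.** For one evenly split binary covariate, SE(log HR) = √(4/deaths). The 95% interval runs from the estimate divided by, to the estimate multiplied by, exp(1.96 × SE). Power uses the Schoenfeld formula at two-sided 5%.

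| Deaths | SE | Interval factor | Power, HR 2 | Power, HR 3 | HR detectable with 80% power |
|---|---|---|---|---|---|
| 6 | 0.82 | 5.0 | 13% | 27% | 9.9 |
| 14 | 0.53 | 2.9 | 25% | 54% | 4.5 |
| 28 | 0.38 | 2.1 | 45% | 83% | 2.9 |

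These are single-covariate figures. Unbalanced covariates, or several fitted together, do worse. For a factor present in 20% of patients (assumed) and without effect, the chance that none of 6 deaths falls in that group is 0.8⁶ = 0.26, and the hazard ratio then has no finite estimate.

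**4. What the p<0.1 screen selects.** To pass, a balanced covariate needs |log HR| above 1.645 × SE:

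- 6 deaths: 1.645 × 0.816 = 1.34, an observed HR of at least 3.8 (or its inverse).
- 14 deaths: 1.645 × 0.535 = 0.88, at least 2.4.
- 28 deaths: 1.645 × 0.378 = 0.62, at least 1.9.

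The number of candidates is not stated. If k candidates were independent and none mattered, 0.1k would pass on average and at least one with probability 1 − 0.9^k: for k = 10, 1.0 and 65%; for k = 20, 2.0 and 88%. These are illustrative, since real candidates are correlated and nominal p-values are unreliable with so few events.

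**5. The other predictor models.** The planning rates imply 141 × 0.30 + 141 × 0.23 = 74.7 Clavien-Dindo ≥3 events and 141 × 0.25 + 141 × 0.19 = 62.0 POPF grade B/C events, enough for about 6 to 7 parameters each at 10 events per parameter. The shortage of events concerns the survival model only.

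**The case against.** The strongest objection is that the death count is not established. The 0–2% is a literature figure for high-volume centers, gives no time window and reads as mortality of the operation. The trial follows patients for 6 months, names ductal adenocarcinoma first among its indications and admits centers doing as few as 10 distal pancreatectomies a year. This stands: a reader might infer that the protocol caps deaths at about six, and it does not. It does not rescue the model, because even the assumed 10% supports only 2 to 3 parameters at 10 events each (5 to 6 at five each), while the rule sets no limit.

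A second objection is that the models are exploratory and that the article promises a detailed analysis plan before database lock, where covariates are normally fixed. It lowers the stakes. But the article does not leave entry open: it states the p<0.1 rule, and that rule is the problem.

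Third, R0 resection may be defined in Additional file 1, the full protocol or the Dutch audit registry on which outcomes are based, none of which is shown. That is fair. A reader might infer that an R0 analysis would be invalid, or that the text was carried over from an oncology trial. Nothing in the document shows either, and tumors are among the included indications. What remains is that the article's own sections disagree. The same holds for survival: the analysis section calls it an endpoint, so it is too strong to say that it is not one, but the endpoint list omits it.

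**Conclusion.** The concern holds for the Cox model. On the document's only mortality figure there would be 0 to 6 deaths among 282 patients; on assumed 6-month rates of 3–10%, about 8 to 28. Uncapped p<0.1 entry is unsuitable across that whole range. This rests on the assumed rates and on the events-per-parameter rule of thumb; the laxer rule of five does not change the conclusion about an uncapped model.

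It would be wrong to extend this to all the predictor analyses in the section. The p<0.1 rule is stated for the Cox regression only, and the Clavien-Dindo and POPF models have enough expected events for a modest covariate set. For R0 resection and survival the defect is an inconsistency between sections, not a demonstrated invalid analysis. The primary non-inferiority conclusion and the sample size are not touched.

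**What to change.** - Remove the multivariable Cox model and its p<0.1 entry rule. Alternatively, keep it as an analysis labelled exploratory, with a few covariates named in advance and their number tied to the observed deaths, for example no more than one parameter per 10 deaths and no model below 10.
- Report in-hospital, 90-day and 6-month deaths as counts by arm with exact confidence intervals.
- Reconcile the Statistical analysis section with the endpoint sections: either list survival and R0 resection as outcomes, giving the analysis population for R0, or remove them from the analysis text.

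The cost is a change of wording and somewhat less analysis. What is lost is an exploratory model that could not be estimated reliably.
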